The other randomised control trial showed that women who used the peanut ball during labour had clinically significant lower caesarean section rates, lower instrumental births including forceps and vacuum births, and lower third and fourth degree perineal laceration rates. Even though the findings were clinically significant, they were not statistically significant. There was no difference in the length of stages of labour [15]. One of the randomised control trials showed that using the peanut ball was associated with a significantly lower incidence of caesarean surgery (OR = 0.41, *p* = .04) and is potentially a successful intervention to help progress labour and support vaginal birth for women labouring with an epidural anaesthesia. A small group of nonrandomized labouring women with an epidural who used a peanut ball (*n* = 30) were compared to those who did not (*n* = 22). Lengths of first and second stages of labour were recorded. Results demonstrated a 46-min reduction in first-stage labour and an 11-min reduction in second-stage labour with women who used the peanut ball [13].

The main aim of this pilot study is to assess the feasibility and practicality of conducting and replicating this trial to a definitive randomised controlled trial (RCT) in terms of the rate of willingness to be randomised, retention or attrition rate, staying in the allocated group and reasons for ceasing to use the peanut ball. Data will also be collected on the likely primary and secondary outcome measures to ensure appropriate powering of the future definitive RCT and the minimum clinically important differences between the control and intervention groups. The secondary objectives will investigate completion and acceptability of the health and satisfaction surveys by women who use the peanut ball and all women about their general level of health. Descriptive statistics will be analysed to show key clinical outcomes and the Mann-Whitney *U* and chi-square analyses for differences between the control and intervention groups that will demonstrate an effect size to calculate the appropriate sample size for the definitive RCT. Analyses will be performed blind to group allocation. The study will also include economic measures for costs and health-related quality of life to assess the feasibility of conducting an economic evaluation in a future definitive trial.

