### Setting, recruitment and informed consent

The trial intervention will be conducted in Sydney, Australia, at the Centre for Nursing and Midwifery Research, Nepean hospital, Western Sydney University. The major sites for this pilot study are the Blue Mountains Anzac District Memorial and Lithgow hospitals. Pregnant primiparous (having first baby) and multiparous (having subsequent baby) women who are labouring with an epidural at the Blue Mountains Anzac District Memorial and Lithgow hospitals will be included in the study.

The participants will be identified and approached and consented during labour if they have an epidural.

The women who fit the inclusion criteria will be provided a participant information sheet and then asked to sign a participant consent by the midwife not involved in her care. Once the woman has consented to the project, she has the opportunity to withdraw from the project at any time throughout the course of the project, and not be penalised. The consent will be placed in a research box in the birthing suite by the midwife so that the researcher will be able to recontact the woman to complete an online survey if she used the peanut ball.

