Midwives will record in the Peanut Ball Research Notebook in the birthing unit if the woman changes her mind if she is allocated to the control or intervention group and decides to change to the other group other than the group she has been allocated. It is important to achieve an “intention to treat analysis” and that participants are analysed according to the group they are originally allocated [19].
*To determine why women stopped using the peanut ball*
The Coordinating Investigator will access the Electronic Medical Record to assess why the woman stopped using the peanut ball. It is important to achieve an “intention to treat analysis” to determine whether or not they adhered to or accepted the intervention. The importance of reporting of numbers and the reasons why participants were lost to follow up is necessary to assess the extent to what the intention to treat may lead to and provide an underestimate of the efficacy of the intervention under ideal circumstances [19].
*To assess likely primary and secondary outcome measures to inform sampling size and powering of the definitive RCT*
The main purpose of this pilot study is to assess the feasibility of conducting a full definitive trial and not to generate statistically significant results. Nonetheless, a secondary aim is to inform the sample size calculation to design a full definitive trial. This requires an estimate of a clinically meaningful effect size and variance that can be entered into a sample size calculation. The key primary clinical outcome is the rate of vaginal births, and the key secondary outcome is the length of labour. For this pilot study, a decision was taken to opt for 50 pregnant women (25 in each trial arm) to inform this process. Indeed, a previous pilot study that investigated the use of the peanut ball with similar aims determined that this sample size may actually be sufficient to demonstrate statistically significant findings [13]. Therefore, given the high feasibility of recruiting these numbers of women at the study sites, a decision was then made to aim for 50 pregnant women in total (as a minimum), and so opt for a comprehensive pilot trial to ensure the pilot can confidently test feasibility and also inform the powering of a future definitive trial.

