#### Secondary objectives

*To investigate completion of the health and satisfaction surveys*

Health and satisfaction surveysThe Health Questionnaire (EQ-5D) will provide important general physical and mental health information about mobility, self-care, usual activities, (for example, work, study, housework, family or leisure activities), pain, discomfort, anxiety, and depression. EQ-5D is a standardised measure of health status developed by the EuroQol Group in order to provide a simple, generic measure of health for clinical and economic appraisal. The EuroQol Group is a network of international multidisciplinary researchers devoted to the measurement of health status [20]. The Health Questionnaire will also request a single score about level of health experienced on that particular day. The first five questions are measured on a Likert scale, and the last question about perception of health asks the respondent to answer on a scale from 0 to 100 with 0 meaning the worst health they can imagine and 100 meaning the best health they can imagine. It is cognitively undemanding, taking only a few minutes to complete. The survey is applicable to a wide range of health conditions and treatments; it provides a simple descriptive profile and a single index value for health status that can be used in the clinical and economic evaluation of health care as well as in population health surveys. The EQ-5D is designed for self-completion by respondents and is ideally suited for use in postal surveys, in clinics and in face-to-face interviews [20].The survey assessing satisfaction levels obtains information in 13 questions about using the peanut ball in Likert scale responses, yes/no answers and free text responses and takes approximately 5 min to complete. The survey will provide a snapshot about the woman’s experience and enquire about the benefits of using the peanut ball, subsequent use of the peanut ball, whether the woman would recommend using the peanut ball to other women and reasons why, discomfort, specific positions used with the peanut ball, experiencing feelings of empowerment and effect on length of labour and demographic details. The survey was developed in alignment with the results of the previous randomised controlled trials [13–15] and as this research only focuses on quantitative data, it was thought that it was beneficial to obtain some information from women about the comfort, perception and satisfaction about using the peanut ball as complementary evidence to the pilot randomised controlled trial. Face validity has been verified by this survey being reviewed and approved by an ethics committee of expert health research professionals in a local health district in NSW, and the survey will be further validated in this pilot study by comparing responses from both sites by using construct validity and establishing appropriate sample size.

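### Comparing answers between the two hospitals does not test the satisfaction survey's construct validity, and ethics committee approval does not verify its face validity

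*Protocol article*

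**What the plan says.** Under Measures used to achieve objectives, Secondary objectives, the protocol article describes a purpose-built satisfaction survey that "obtains information in 13 questions about using the peanut ball in Likert scale responses, yes/no answers and free text responses". Two statements about its validity follow.

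- On what has been done: "Face validity has been verified by this survey being reviewed and approved by an ethics committee of expert health research professionals".
- On what is still to be done: "the survey will be further validated in this pilot study by comparing responses from both sites by using construct validity". The sentence ends by adding that a suitable sample size will be established.

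The article names no construct, no expected relation between the survey and another measure, no expected pattern between the hospitals, and no rule for deciding that validation succeeded.

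The survey goes to ball users only. Setting, recruitment and informed consent says consent forms are kept so that the researcher can "recontact the woman to complete an online survey if she used the peanut ball". The Background separates the two questionnaires in the same way: "completion and acceptability of the health and satisfaction surveys by women who use the peanut ball and all women about their general level of health". On numbers, Measures used to achieve objectives, Primary objectives, says "a decision was taken to opt for 50 pregnant women (25 in each trial arm) to inform this process", and calls 50 a minimum.

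**The concern.** Construct validity asks whether scores behave as theory predicts: whether they correlate with related measures, separate groups known to differ, or show the expected internal structure. Whether two hospitals give similar answers is a different question. The article therefore names a method that does not do the job it is given. This is a misstated method, not detail left to a fuller plan.

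The face-validity sentence has a milder form of the same problem. It offers a committee's approval as completed verification. The article reports no judgement of the items by women who have laboured with the ball or by midwives.

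At stake is what the pilot may conclude about its own instrument. The Discussion already anticipates favourable findings on women's perception, empowerment and comfort. Of the study's measures, this survey is the one that asks about empowerment and about comfort with the ball. If the text stands, a report could call the survey validated on an analysis that could not have shown it.

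**Working it through.** The article gives no power, effect size or pass criterion for the validation, so there is no stated figure to reproduce. The check has a reasoning part, which carries the point, and an illustrative calculation.

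**What each result would mean.**

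- The hospitals give similar answers. This is expected if the items measure satisfaction well and the hospitals are alike. It is equally expected if the items measure nothing.
- The hospitals give different answers. This is expected if the items work and the women or their care differ. It could also arise from an item understood differently at each site.

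Neither result separates a valid instrument from an invalid one, so a larger sample would not repair the test.

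**How many women would answer.** From the article: 50 women as a minimum, 25 per arm, two hospitals, ball users only. That gives about 25 respondents before non-response and crossover. The split between hospitals is not given, so 13 v 12, 18 v 7 and 20 v 5 are assumed.

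**Power for a site difference.** Assumptions: one score, a two-sided 5% test, and a non-significant result taken as support. With d the site difference in SD units, the non-centrality is d × √(n₁n₂/(n₁+n₂)).

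- 13 v 12, d = 0.5: 0.5 × √(156/25) = 1.25. Normal approximation: Φ(1.25 − 1.96) = 24%; t-test 22%.
- 18 v 7, d = 0.5: 0.5 × √(126/25) = 1.12. Normal approximation 20%; t-test 19%.
- 20 v 5, d = 0.5: 0.5 × √(100/25) = 1.00. Normal approximation 17%; t-test 16%.

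The differences detectable with 80% power by t-test are 1.17, 1.30 and 1.46 SD. Detecting 0.5 SD with 80% power needs 2 × (1.96 + 0.84)²/0.5² ≈ 63 respondents per site. If only 17 women responded, split 9 v 8, power for 0.5 SD would be 16% and the detectable difference 1.46 SD.

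**Can the comparison tell a working item from noise?** This was simulated for one 5-point item with a Mann-Whitney test, 5,000 runs per split. The table shows the share of runs with no significant site difference.

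| Split | Random answers | Item tracks its trait, no site difference | Item tracks its trait, 0.5 SD site difference |
|---|---|---|---|
| 13 v 12 | 94.9% | 94.8% | 80.9% |
| 18 v 7 | 95.4% | 95.2% | 83.2% |
| 20 v 5 | 95.1% | 95.3% | 86.2% |

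The first two columns agree to within simulation error: a random item and a working item get the same result. If a site difference were instead taken as the sign of validity, both would almost always fail, which is no more informative.

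**The case against.** The strongest reply is that the article never says that no difference means validated. It sets no test and no threshold, and the full protocol, which is not shown, may supply them. That stands against any firm statement of pass rates, so the power figures above are illustrations. It does not rescue the method, because no threshold turns agreement between two hospitals into evidence of construct validity.

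A reader might infer that the comparison would pass almost any instrument, or that a finding of no difference is close to guaranteed. The article does not support this. The 95% figures are per item, and the survey has 13 questions with no total score described. If, say, 10 closed items were each tested at 5%, were independent and had no true site difference, the chance of at least one significant result would be 1 − 0.95¹⁰ = 40%. Correlated items or conservative small-sample tests would lower it.

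A reader might also take 25 as a ceiling on respondents. It is not. Fifty is a minimum, women allocated to usual care may choose the ball, and the survey follows use of the ball, not allocation. Non-response works the other way.

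A reader might infer that the survey is to become the definitive trial's measure of comfort and empowerment. No section says so. Vaginal birth and length of labour are named as the key clinical outcomes, the survey is described as supplementary, and a questionnaire given only to ball users cannot be a between-arm outcome.

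On face validity, review by health research experts can contribute, and the article says the survey was developed in line with earlier trial results. It would be too strong to say that this step has no bearing on validity. What fails is the claim that approval verified it.

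Finally, the Statistical analysis section already says the pilot is not powered for meaningful tests. That discloses the low power but does not correct the method.

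**Conclusion.** The point holds as a correction of method and wording. A between-site comparison does not test construct validity at any sample size, and ethics committee review does not by itself verify face validity. These two conclusions rest on the article's own sentences and need no numerical assumption.

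The low information is secondary and conditional. It assumes about 25 respondents, the splits shown, a single score and non-significance read as support. On that basis, power for a 0.5 SD site difference is 16% to 22%.

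The consequence is limited. The survey serves a secondary objective, and neither the primary feasibility objectives nor the randomised comparison depends on it. The change is desirable but not essential to the trial.

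**What to change.** Make three wording changes in the Secondary objectives text:

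1. Remove the site comparison as a validity test. If responses by hospital are of interest, report them descriptively.
2. Replace the claim of verified face validity with a statement that the survey was reviewed by an expert committee.
3. Describe the instrument as not validated in this pilot.

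Optionally, report a few associations stated in advance, such as reported discomfort against early stopping of the ball, as exploratory estimates with 95% confidence intervals. This requires survey answers to be linked to clinical records by study code. The article says surveys are de-identified in the database and does not say whether linkage is possible. Such estimates would be imprecise: a correlation of 0.5 with n = 25 has an approximate interval of tanh(0.549 ± 1.96/√22), or 0.13 to 0.75. They would not establish validity either.

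The three wording changes need no new data, and their only downside is a weaker validity claim. The optional analyses cost whatever linkage requires.

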### Statistical analysis

#### Quantitative data

In terms of the women’s willingness of being randomised into the control or intervention group and assessment of recruitment and attrition rates and staying in the allocated groups, the Coordinating Investigator will access this information from the Peanut Ball Research Notebook and assess the sample size. This information will be estimated as accurately as possible from the critical parameters we wish to estimate [19, 22] that includes the minimum important differences when comparing the means of continuous outcomes and categorical outcomes between the intervention and control groups. The differences between the vaginal birth rate (assessment of likely primary outcome for definitive RCT) and the length of labour (assessment of likely secondary outcome for definitive RCT) will be analysed. Demographics will be reported using descriptive statistics. The Coordinating Investigator will also access women lost to follow up and if women stopped using the peanut ball from the Electronic Medical Record.

The purpose of the pilot is to assess the feasibility of the component elements together to inform a definitive trial. The pilot and sample size of 50 is not intended to be powered to conduct meaningful statistical tests [19]. Nonetheless, and for exposition purposes, standard tests will be conducted and reported. Online survey results will provide complementary data from the woman’s perspective of using the peanut ball during labour and health and quality of life.

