**Methods:**

A minimum number of 50 women (25 in each trial arm), who are using an epidural in labour at two hospitals in NSW over a 1-year period, will be recruited and randomly allocated into a group that uses the peanut ball or into a group that does not use the peanut ball. Primary study objectives include assessing the proportion of women willing to be randomised, retention/attrition rates, and with associated reasons. Data will be collected on key clinical outcomes (natural birth rate, length of stay) with means and variances estimated between trial arms. This will inform the appropriate powering of a future definitive RCT. Secondary study objectives will include investigating the completion and acceptability of health and satisfaction surveys and assess the feasibility of conducting an economic evaluation alongside a future trial.

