Both surveys will be distributed to the respondents from an electronic platform—Qualtrics [21] platform—and have been electronically tested to assess the functionality prior to distribution of the online survey. Each survey will be distributed to the participant’s email and de-identified in the computer database. All surveys will be analysed, including those not completed. All of the data collected in this closed survey will be stored in a password-protected computer and will only be accessible by the researchers.
*To assess the feasibility of conducting an economic evaluation alongside a future definitive trial*
The feasibility of collecting data required for an economic evaluation will be tested. For this pilot, we will collect information on health service usage between trial arms, including staff time, medications, procedures and length of stay in hospital. The inclusion of the EQ5D5L will assess the feasibility of incorporating an economic measure of HRQoL, where responses will be converted into ‘health utilities’.
*To measure key clinical outcomes and differences between the control and intervention group*
Details about other birth outcomes will also be collected to determine the baby’s condition, perineal damage, other methods of pain relief used, position of mother and baby during labour, blood loss, cervical dilatation at time of insertion of epidural and evidence of augmentation and/or induction of labour.

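### Mann-Whitney U and chi-square tests are named as the route to the definitive trial's effect size, a job that tests on 50 women cannot do; between-arm differences with intervals should take their place

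*Protocol article*

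**What the plan says.** Four places in the protocol article bear on this.

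- **Background, paragraph on aims.** After promising descriptive statistics for the key clinical outcomes, it turns to two tests, of which the Mann-Whitney U is named first. The sentence continues: "chi-square analyses for differences between the control and intervention groups that will demonstrate an effect size to calculate the appropriate sample size". The trial to be sized in this way is the definitive one.
- **Statistical analysis, Quantitative data.** "The pilot and sample size of 50 is not intended to be powered to conduct meaningful statistical tests". The next sentence reads: "Nonetheless, and for exposition purposes, standard tests will be conducted and reported". This section also says that the differences in vaginal birth rate and in length of labour will be analysed.
- **Measures used to achieve objectives, Primary objectives.** The sizing step is said to need an effect size that matters clinically, and a variance. "The key primary clinical outcome is the rate of vaginal births, and the key secondary outcome is the length of labour". On numbers, "a decision was taken to opt for 50 pregnant women (25 in each trial arm) to inform this process". The same paragraph says that significant results are not the purpose, but also that an earlier peanut ball pilot suggests this size might be enough to produce them.
- **Abstract, Methods.** Key clinical outcomes will be collected "with means and variances estimated between trial arms".

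**The concern.** The two statements about the tests do not fit together. In the Statistical analysis section they are unpowered and there for illustration. In the Background they are the tool that yields a design input for the next trial. A procedure that the plan itself calls not meaningful at this size should not supply that input.

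The tests also have the wrong output for the job. A Mann-Whitney U test compares ranks, so it returns neither a difference in hours of labour nor an SD. A chi-square test returns a statistic and a p-value, not a control-arm rate or a rate difference with its uncertainty. A clinically important difference is a judgement made beforehand, and no test on pilot data can produce it.

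Two things are at stake. If the observed or significant pilot difference is carried into the sample-size formula, the definitive trial may be far too small or may be wrongly abandoned. And p-values reported over several outcomes can produce a chance finding that is read as evidence, in an article whose Discussion already expects better outcomes in the peanut ball arm.

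**Working it through.** **Inputs.** From the document: 25 women per arm, and two key outcomes (vaginal birth rate, length of labour). Not stated, so assumed here: two-sided 5% level per test, no adjustment, vaginal birth rates of 60% to 80%. The figure of 50 is a decision and not a calculation, so there is no sample-size figure to reproduce.

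**1. Precision that a p-value leaves out.** The 95% half-width for a rate difference, with a common rate p, is 1.96 × √(2p(1 − p)/25).
- p = 0.80: 1.96 × √0.0128 = 0.222
- p = 0.70: 1.96 × √0.0168 = 0.254
- p = 0.60: 1.96 × √0.0192 = 0.272

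For a continuous outcome such as length of labour, the half-width is 1.96 × √(2/25) = 0.55 SD. The pooled SD (48 degrees of freedom) has a 95% interval of about 0.83 to 1.25 times its estimate.

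**2. What this means for sizing.** Suppose that the pilot shows 60% v 80%. The half-width is 1.96 × √((0.24 + 0.16)/25) = 0.248, so the difference is 20 ± 25 points. True differences of 10 and of 20 points both fit. At 80% power, with n = [1.96√(2p̄(1 − p̄)) + 0.842√(p₁(1 − p₁) + p₂(1 − p₂))]² / (p₁ − p₂)²:
- 60% v 80%: 82 per arm
- 60% v 70%: 356 per arm

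The required size differs by a factor of 356/82 = 4.3. The pilot's own power is 34% in the first case and 11% in the second.

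**3. What significance would select.** Take 15/25 vaginal births in the control arm. The uncorrected chi-square is:
- against 21/25: 50 × 150² / (25 × 25 × 36 × 14) = 3.57, p about 0.06
- against 22/25: 50 × 175² / (25 × 25 × 37 × 13) = 5.09, p about 0.02

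So no gain smaller than 28 points would reach 5%. An effect that is read off because it is significant would be very large.

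**4. False positives when nothing differs.** For k independent tests the chance of at least one is 1 − 0.95^k.
- The two key outcomes: 1 − 0.95² = 9.75%
- Twelve outcomes: 1 − 0.95¹² = 46.0%

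The figure of twelve is a scenario. The Secondary objectives text lists further items such as "perineal damage, other methods of pain relief used, position of mother and baby during labour, blood loss, cervical dilatation at time of insertion of epidural". The objective there covers between-arm differences, but no list of tests is given. Depending on which items are counted, the list runs from about 9 to 15. The scenario was simulated with 4,000 null pilots per setting, 25 per arm, five Mann-Whitney and seven chi-square tests, assumed binary rates of 0.1 to 0.7, and equal correlation between outcomes:

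| Correlation | Chi-square uncorrected | Continuity-corrected |
|---|---|---|
| 0 | 49% | 35% |
| 0.2 | 46% | 33% |
| 0.3 | 44% | 31% |
| 0.5 | 41% | 26% |
| 0.7 | 32% | 22% |

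The range is therefore roughly 20% to 50%.

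**The case against.** **The planning quantities are in the plan.** The Abstract promises means and variances by arm, the Statistical analysis section names the differences in the two key outcomes, and the Background sentence opens with descriptive statistics. This stands. A reader might infer that the pilot will yield no usable planning inputs, and the document does not support that. What remains is the role that the Background gives to the tests, and the lack of intervals in either section.

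**The tests are openly labelled.** They are called unpowered and for exposition, and no stated decision turns on a p-value. This softens the point. It does not remove it, because the Background gives the same tests a purpose beyond exposition.

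**About half of null pilots would show a significant result.** A reader might infer this from the list of outcomes. It needs a 5% level that the article does not state, about 13 tests that it does not list, near-independence between related birth outcomes, and an uncorrected chi-square. Some items do not belong in such a count. The mother's position is part of the intervention. Cervical dilatation at epidural insertion precedes randomisation. For the economic items the text says only that "we will collect information on health service usage between trial arms, including staff time, medications, procedures and length of stay in hospital", in order to check feasibility, and no test of them or of the EQ-5D is stated.

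**No multiplicity rule is given.** The significance level, any adjustment and the test list may stand in the full protocol or in an analysis plan, neither of which is shown. Their absence from a journal article is not a finding.

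**A rank test does carry an effect size of a kind.** U divided by 25 × 25 estimates the probability that a woman in one arm has the longer labour. That is true, but it is neither a difference in hours nor the variance that the article says it needs.

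**Conclusion.** The point holds as a wrongly assigned method. The Background gives hypothesis tests the task of supplying the effect size. The Statistical analysis section says that the sample cannot support meaningful tests, and the Primary objectives text asks for quantities that these tests do not return.

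Its size is best seen in the precision: about ±22 to ±27 points on the vaginal birth rate difference (assumed rates 80% to 60%), wide enough to cover designs that differ more than fourfold in size. The false-positive risk is secondary. It is about 10% for the two outcomes that the analysis section names, and roughly 20% to 50% only if about 12 are tested, all at an assumed 5% level.

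The defect does not require a ban on every p-value. It requires that the tests stop feeding the sample-size step and stop being the main between-arm result.

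**What to change.** Reword the aims paragraph of the Background and the Quantitative data section as follows.

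1. The reported between-arm results are arm summaries (rate, or mean and SD) and differences with 95% intervals, for example Newcombe intervals for rates and bootstrap intervals for mean differences.
2. The definitive trial will be sized from a clinically important difference fixed beforehand, combined with the pilot's control-arm rate and SD and their uncertainty. The observed pilot difference and its p-value are not used for this.
3. The hypothesis tests are dropped, or are limited to vaginal birth and length of labour, labelled exploratory and kept out of the sizing step.

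The cost is wording in two places, with the same data and similar analysis work. The article reports that recruitment had not begun, so no collected data are affected. The downside is fewer p-values to quote, or none.
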